#### Blinding

Assessors performing the evaluations and investigators will be blinded to group allocation. The statistician will be blinded until completion of the statistical analyses. Only the kinesiologists executing the weekly follow up of exercise/cognitive training program will be aware of the assigned intervention. Kinesiologists will not take part in any assessment.

## Discussion

The latest WHO Guidelines on physical activity and sedentary behavior recommends for adults and older adults with chronic conditions, such as CVD, at least 150–300 min of moderate-intensity aerobic physical activity, or at least 75–150 min of vigorous intensity aerobic physical activity, or an equivalent combination of moderate- and vigorous-intensity activity throughout the week (30). With the COVID-19 crisis and the confinement measures in place (e.g., closed gyms), these recommendations are difficult to meet (1, 38, 39). Among the 1,098 Canadian adults included in the study by Lesser et al., 40% of inactive individuals became less active during the restrictions of daily living caused by the COVID-19 pandemic (39). In cardiac patients, who already tend to have a sedentary/inactive profile, the confinement measures excessively increase the level of physical inactivity and sedentary lifestyle, which can further deteriorate cardiovascular health and increase the risk of acute events (4). Frail individuals, older adults, and individuals with chronic conditions such as CVD are at higher risk to suffer from the direct and collateral consequences of the COVID-19 pandemic. Hence, allowing older adults with CVD to maintain and/or improve their cognitive and physical health may help to prevent a possible secondary crisis caused by the long-term alteration of their health condition. Our home prevention strategies allow patients, including those living in remote areas, to have cognitive and physical stimulation for 6 months.

Exercise and cognitive training separately have demonstrated enhancements of multiple and specific aspects of cognitive and physical functions and could have a synergistic effect on cognition in healthy older adults (15). Individuals with CVD who participated in a CR program improve their cognitive performances (12). In addition, the synergistic effect of exercise associated with cognitive training on cognition has never been shown in older adults with CVD. Thus, some questions need to be addressed regarding how much benefits can be gained by adding cognitive training to physical exercise and regarding the optimal dose of each type of intervention.

This trial proposes crisis-adapted lifestyle interventions and remote assessments. More precisely, to further ensure the continuity and the regularity of the exercise training, the proposed trial offers weekly phone call support and an online video training program, providing a wide range of exercises to help participants maintain their exercise routine even during the lockdown. In CVD, among the patients who complete a phase II center-based CR about half of the patients tend to return to their previous lifestyle habits, become sedentary again after a few months, and are non-adherent to physical activity target levels recommended by physicians (40, 41). Home environment with regular contact with telephone support or videoconference from the medical or research team may be more likely to help sustain positive physical and psychosocial changes over time, compared to institution-based programs (42–44).

Most participants in exercise clinical trials come from urban areas, which likely limits generalization of findings, and individuals from rural communities are still underrepresented (45). Home-based interventions, made available for all, would address this problem, and offer a great solution to counteract sedentary/inactivity behavior in the COVID-19 pandemic situation. A home-based combined intervention with exercise and cognitive training could help to maintain and enhance cognition and cardiovascular health in older adults with CVD who could no longer access training facilities during the COVID-19 lockdown.

### Study Limitations

Some limitations of our trial need to be mentioned. First, our design does not include a control group without intervention. Because of the pandemic context, some ethical considerations refrained the research team from implementing a control group without any intervention. However, to partially address this limitation, in our analysis we will take into account the dose response effect as a function of the volume of training performed by participants. Based on the nature of each activity, its intensity and its frequency, a weekly dose of physical exercise (converted in kcal and in METs using the Compendium of Physical Activities) will be computed. The effect of physical exercise dose on cognitive and physical functions will be evaluated according to participant's mean weekly dose during the 6 months of intervention. Based on the overall study sample distribution, participants could be classified into “higher,” “medium,” and “lower” doses of physical exercise (i.e., tercile split).

Secondly, our participants do not have precise control of the intensity and duration of the exercise sessions (heart rate monitors, pedometers, or other tools). This is only declarative data reported weekly with the kinesiologists. Our study focuses on exercise and cognitive training in CR's phase III and should not be confused with a comprehensive CR program delivered in phase II. Adherence to medication, diet and appropriate teaching about patient's risk factors and CVD are critical aspects of a comprehensive CR program (phase II). Consequently, we will include some patients who have completed a CR program and others who have not benefited from this program. Then, non-exercise prediction of cardiorespiratory fitness with an equation is valid for healthy individuals, but little is known about its reliability in patients with CVD. Moreover, variability was observed in the accuracy between non-exercise prediction equations and the ability of equations to detect changes in cardiorespiratory fitness (46). Therefore, the use of non-exercise prediction equations could lead to a significant error in the estimated change of participants' cardiorespiratory fitness. Finally, sex was not taken into account in recruitment and randomization processes, although sex differences have been reported on cognition (47), as well as in exercise-training effects on cognition in healthy older adults (48). No study to date has documented potential sex-related differences with regards to the effects of exercise, cognitive or combined training on cognition and physical outcomes in older adults with CVD. Given the sex-related differences in cognition, exercise intervention effects and diseases, sex differences are to be expected in the present study.

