##### Exercise Monitoring

Participants will be encouraged to complete a home-based physical exercise using video capsules available via Facebook or Youtube, created by the Centre EPIC of the MHI's team of kinesiologists (20). Aerobic, muscular strengthening, flexibility, and/or balance exercises are proposed in these videos, and do not require any equipment. Each video lasts ~15 min and includes a 5-min warm-up, followed by a 10-min training, and finally by a 2-min cool-down period. Guidelines are provided by kinesiologists to allow participants to adapt the exercise to their physical capacities. Participants will be invited to perform exercise sessions at least 5 times a week. The exercise sessions can be performed at home using the video capsules, or with other video or web-based training programs. Participants can also engage in outdoor activities (e.g., walking or cycling). To track their adherence, the duration, intensity, and nature of the activity of each training session will be reported by the participant in a journal, that they will transmit to their training coach during their weekly follow-up call. The Borg Rating of Perceived Exertion (RPE) graduated from 0 to 10 will be used by participants to assess the intensity of their exercise sessions.

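### The exercise dose-response analysis is self-selected and self-reported, so it cannot partly stand in for the missing control group; its listed inputs also omit session duration

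*Protocol article*

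**What the plan says.** All references are to the protocol article.

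- **Study Limitations, role of the analysis.** The section states that "our design does not include a control group without intervention" and offers a remedy: "to partially address this limitation, in our analysis we will take into account the dose response effect". The same sentence ties this to training volume rather than to allocation.
- **Study Limitations, definition of dose.** The inputs are listed in these words: "Based on the nature of each activity, its intensity and its frequency, a weekly dose of physical exercise". The result is "converted in kcal and in METs using the Compendium of Physical Activities". Its effect on cognitive and physical function is to be evaluated using each participant's weekly mean over the six-month intervention.
- **Study Limitations, grouping.** From the distribution in the whole sample, "participants could be classified into “higher,” “medium,” and “lower” doses of physical exercise (i.e., tercile split").
- **Study Limitations, data quality.** On the intensity and duration of sessions: "This is only declarative data reported weekly with the kinesiologists".
- **Exercise Monitoring.** Participants are invited to exercise at least five times a week and may use the study videos, other programmes or outdoor activity. For each session, "the duration, intensity, and nature of the activity of each training session will be reported by the participant in a journal".
- **Statistical Analysis.** The model for cognitive change adjusts for age, sex and education, and secondary and exploratory outcomes follow the same model. No other covariates are named.

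**The concern.** A no-intervention group would show how much cognition changes over six months without the programme, including practice on repeated tests, the passage of time and the changing pandemic. The dose-response analysis is credited with supplying part of that. It cannot, for two reasons.

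First, dose is not assigned. It is a behaviour that follows randomisation, chosen and logged by the participant. People who are healthier, already active or more motivated are likely to log more, and declining health during follow-up can lower both exercise and test performance. In the combined arm, diligent exercisers may also be diligent cognitive trainers, and the dose groups would pool the arms.

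Second, a change common to everyone cancels out of a comparison between higher and lower doses. That comparison neither estimates it nor removes it from the pre-post change. Recovering it would mean extrapolating to zero exercise, which the design does not set out to observe, and assuming no confounding.

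At stake is interpretation: the article speaks of the effect of exercise dose, and a selection gradient could be reported under that name.

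The dose definition raises a smaller matter. Taken literally, the listed inputs would score long and short sessions alike.

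**Working it through.** **1. The plan's own figure.** The article gives no figure for the dose analysis. Its Sample Size Calculation supplies the scale used below: a difference of 0.186 and a common SD of 0.325, with a two-sided 5% t-test and 80% power. The standardised difference is 0.186 / 0.325 = 0.572, which needs 48.9, so 49 per arm (power at 49: 80.1%). The stated 49 reproduces. It supports the randomised comparison only.

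**2. Spacing of terciles.** For a standard normal dose, the upper cut point is 0.431 and the density there is 0.3636. The mean of the top third is 0.3636 / (1/3) = 1.091, and that of the bottom third is −1.091.

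**3. Information lost by terciles.** Information retained on a linear trend = (2/3) × 1.091² = 0.793. About 21% is lost.

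**4. Spurious gradient when exercise has no effect.** Suppose one unmeasured factor correlates r₁ with dose and r₂ with cognitive change. The expected top-minus-bottom gap in SD units is r₁ × r₂ × 2 × 1.091; multiply by 0.325 for z units. The correlations are assumptions, because the article gives none. The last column is the two-sample t-test power for that gap with 98 / 3, about 33 per tercile (98 = 2 × 49 completers).

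| r₁ / r₂ (assumed) | Gap, SD | Gap, z | Chance of p < 0.05 |
|---|---|---|---|
| 0.2 / 0.2 | 0.087 | 0.028 | about 6% |
| 0.3 / 0.3 | 0.196 | 0.064 | about 12% |
| 0.4 / 0.3 | 0.262 | 0.085 | about 18% |

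Without confounding the last column would be 5%. For scale, the assumed mean for exercise alone in the Sample Size Calculation is 0.239, so the middle row is 0.064 / 0.239 = 27% of it. The 0.186 is the difference assumed for adding cognitive training, so it is not the yardstick for an exercise-dose effect.

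**5. Duration.** The passages compare as follows.

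| Place | Treatment of duration |
|---|---|
| Exercise Monitoring | Recorded for every session |
| Study Limitations, purpose of the analysis | Implied by volume of training |
| Study Limitations, list of dose inputs | Not listed |
| Study Limitations, conversion to kcal | Required, since energy spent depends on time |

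Taken literally, five weekly sessions at an assumed 4 METs would score the same whether they lasted 15, 30 or 60 minutes. The actual loads would be 5 × 4 × 15 = 300, 5 × 4 × 30 = 600 and 5 × 4 × 60 = 1,200 MET-minutes, a fourfold range. The kcal conversion contradicts that literal reading.

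**The case against.** The strongest defence is that the article claims little. It says only that the limitation is partially addressed, places this among its limitations and discloses that the exercise data are declarative. Dose enters neither stated hypothesis test: the primary one rests on pre-post change and the secondary one on the randomised interaction. The outcome is change from baseline, so baseline differences in cognitive level alone need not create a gradient. Choice of covariates and functional form can be left to an analysis plan that is not shown.

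Much of this stands. A dose gradient can be supportive exploratory evidence, and nothing in the article says it would prove efficacy. But even a partial remedy credits the analysis with a control-group function, and change scores do not remove factors that drive both exercise and subsequent change.

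Three stronger readings are tempting and not supported:

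- **That terciles are the planned analysis.** They are worded as something that could be done. The firm commitment, to evaluate effects by mean weekly dose, is compatible with a continuous model.
- **That dose will be computed without duration.** Volume and kcal both need time, and duration is recorded, so a word missing from one sentence is the likelier explanation.
- **That a bias of known size has been shown.** The correlations in the table are assumed, and at these values a spurious gradient would usually not reach significance.

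**Conclusion.** The point holds in limited form. The dose-response analysis is a non-randomised comparison of self-chosen, self-reported exposure. It does not replace any part of a no-intervention control, and the covariates named in the article do not cover the obvious confounders. The size of a spurious gradient is unknown; the figures of about 0.03 to 0.085 z assume a single confounder with correlations of 0.2/0.2 to 0.4/0.3, a normally distributed dose and an SD of 0.325. The 21% information loss applies only if terciles are used for the analysis and dose is roughly normal. The missing duration is an inconsistency to reconcile, not evidence of a missing measurement. A reader might infer that the trial's main comparison is compromised; it is not, because neither the randomised between-arm contrast nor its sample size depends on the dose analysis.

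**What to change.** 1. Reconcile the dose definition in Study Limitations with Exercise Monitoring by stating that the mean weekly dose uses recorded session duration, for example as MET-minutes.
2. Analyse dose as a continuous variable, adjusted for arm, baseline cognitive score, baseline physical activity (Physical Activity Scale for the Elderly), age, sex and education. Keep terciles for display only.
3. Label the result an exploratory, non-randomised association based on self-report.
4. Remove the statement that it partially addresses the missing control group.

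The cost is a few sentences of wording and a modest extra analysis. Every variable is already collected: duration in the participant journal, and cognition, the activity scale and demographics at baseline. No new data or additional participants are needed.

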### Trial Status

The COVEPICARDIO study is the fourth version of the protocol validated by the Research Ethics Board of Montreal Heart Institute in October 2020. Recruitment for the study started May 20, 2020 and is planned to be finished in September 2021.

## Ethics Statement

The study protocol was approved by the Montreal Heart Institute's (MHI) Research Ethics Board (FWA00003235; research project: ICM 2020-2785). All participants will provide informed consent prior to starting the study.

